### Data description

Normally distributed continuous variables will be expressed as the means ± standard error of the mean (SEM), abnormally distributed continuous variables will be expressed as medians and interquartile ranges, and categorical variables will be expressed as numbers and percentages.

### Outcome analysis

For the primary outcome, the proportions of patients who developed off-therapy relapse in each group will be compared with the Pearson chi-square method. Time to event analysis will be performed with the Kaplan-Meier method. For the secondary outcomes, the data are continuous variables, for which we will use repeated-measures mixed effects models to test differences between the groups. The total effect of the scale scores from questionnaires will be tested with the Wilcoxon rank sum test. A paired *t* test will be used for comparisons of data before and after treatment within groups. A two-sided *p* value < 0.05 will be considered statistically significant; confidence intervals (CIs) are set at 95%.

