## Interviews

From the first day to the observation point of week 96, we will follow up patients every 24 weeks (± 3 days) and dispatch trial drugs on each visit. In addition, we will retrieve the empty boxes and the remaining doses of each patient for verification and recording. At the end of week 96, patients will be informed again about the potential risks of stopping NA therapy, and additional consent to participate in off-therapy observation will be required. From week 96 to week 120, we will set the intervals between interviews to 4 weeks (± 3 days).

Specimens collected during the trial will be stored in the Biobank of Dongzhimen Hospital. The specimens will be used to reconfirm the readings of existing assessments if necessary, as well as for genetic or molecular analysis in current trials and for future use in ancillary studies.

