## Assessments

To ensure safety and reveal the curative effects of trial drugs, patients will be monitored regularly with assessments throughout the trial (Table 1).

**Table 1 Tab1:** Scheduled assessments

Assessment	Consolidation therapy									Off-therapy observation						Treatment after recurrence
	Day 1	12 w	24 w	36 w	48 w	60 w	72 w	84 w	96 w	4 w	8 w	12 w	16 w	20 w	24 w	Recurrence
**Blood, urinary, and stool routine test**	**√**		**√**		**√**		**√**		**√**						**√**	
**Liver functions**	**√**		**√**		**√**		**√**		**√**	**√**	**√**	**√**	**√**	**√**	**√**	**√**
**Renal function**	**√**		**√**		**√**		**√**		**√**						**√**	
**HBV-serum marker**	**√**		**√**		**√**		**√**		**√**			**√**			**√**	**√**
**HBV DNA**	**√**		**√**		**√**		**√**		**√**	**√**	**√**	**√**	**√**	**√**	**√**	**√**
**Liver biopsy**	**√**								**√**							
**ccc DNA**	**√**								**√**							
**HBcrAg**	**√**		**√**		**√**		**√**		**√**			**√**			**√**	
**HBV pregenomic RNA**	**√**		**√**		**√**		**√**		**√**			**√**			**√**	
**LHBs**	**√**		**√**		**√**		**√**		**√**			**√**			**√**	
**AFP**	**√**		**√**		**√**		**√**		**√**						**√**	
**PT**										**√**	**√**	**√**	**√**	**√**	**√**	
**ECG**	**√**		**√**		**√**		**√**		**√**						**√**	
**Abdominal ultrasound scan**	**√**		**√**		**√**		**√**		**√**						**√**	
**Antibodies of hepatitis A, C, D, E**	**√**															
**CLDQ**	**√**	**√**	**√**	**√**	**√**	**√**	**√**	**√**	**√**			**√**			**√**	
**SF-36**	**√**	**√**	**√**	**√**	**√**	**√**	**√**	**√**	**√**			**√**			**√**	
**The symptom score of TCM**	**√**	**√**	**√**	**√**	**√**	**√**	**√**	**√**	**√**			**√**			**√**	

Patients will be followed up every 12 weeks during the consolidation therapy and every 4 weeks in the off-therapy observation (“w” is short for “weeks”)

*Abbreviations*: *HBV* hepatitis B virus, *ccc DNA* covalently closed circular DNA, *HBcrAg* hepatitis B core-related antigen, *LHBs* HBV large surface proteins, *AFP* alpha fetoprotein, *PT* prothrombin time, *ECG* electrocardiogram, *SF-36* the Short Form (36-item) Health Survey, *CLDQ* the Chronic Liver Disease Questionnaire

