## Secondary outcomes

Secondary outcome measurements include virus serological indicators, HBV DNA, liver function, liver biopsy results, cccDNA, hepatitis B core-related antigen (HBcrAg), HBV pregenome RNA (pgRNA), HBV large surface proteins (LHBs), the symptom score of TCM, the Short Form (36-item) Health Survey (SF-36), and the Chronic Liver Disease Questionnaire (CLDQ).

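### SF-36 and CLDQ fall under both a mixed-model rule and a Wilcoxon rank sum rule, with no statement of which governs; the rank test would be less precise than a baseline-adjusted model

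*Protocol article*

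**What the plan says.** All references are to the protocol article.

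- **Secondary outcomes** ends its list with "the symptom score of TCM, the Short Form (36-item) Health Survey (SF-36), and the Chronic Liver Disease Questionnaire (CLDQ").
- **Outcome analysis** gives a general rule: "For the secondary outcomes, the data are continuous variables, for which we will use repeated-measures mixed effects models to test differences between the groups". No exception is stated.
- The next sentence there gives a rule for questionnaires: "The total effect of the scale scores from questionnaires will be tested with the Wilcoxon rank sum test".
- The only before-and-after comparison named is within groups: a paired t "test will be used for comparisons of data before and after treatment within groups".
- The same section sets the level for all tests and intervals: a two-sided p "value < 0.05 will be considered statistically significant; confidence intervals (CIs) are set at 95"%.
- **Assessments, Table 1** schedules CLDQ, SF-36 and the TCM symptom score on Day 1, at weeks 12 to 96 in steps of 12, and at off-therapy weeks 12 and 24. Its footnote reads: "Patients will be followed up every 12 weeks during the consolidation therapy and every 4 weeks in the off-therapy observation".
- **Interviews** gives a different interval up to week 96: "we will follow up patients every 24 weeks (± 3 days) and dispatch trial drugs on each visit".

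**The concern.** SF-36 and CLDQ are secondary outcomes and are also questionnaire scales, so both sentences cover them. Nothing ranks one sentence above the other. The total effect is not defined, nor is the visit tested, nor whether the raw score or the change from Day 1 is ranked. A test that is not fixed in advance leaves room to choose after the results are known. Keeping allocation concealed from the analysts until the trial ends reduces that room but does not close it.

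If the Wilcoxon test is the one intended, there is a second cost. A two-sample rank sum test takes one number per patient and no covariate. The trial collects a Day 1 score and a series of later scores, and the main patient-reported comparison would leave much of that information unused.

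**Working it through.** **Which outcomes fall under which rule**

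| Score | Mixed-model sentence | Wilcoxon sentence |
|---|---|---|
| SF-36 | yes, a secondary outcome | yes, a questionnaire scale |
| CLDQ | yes, a secondary outcome | yes, a questionnaire scale |
| TCM symptom score | yes, a secondary outcome | unclear; it is not called a questionnaire |

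**How many scores per patient**

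Table 1 gives 1 baseline + 8 on-treatment + 2 off-therapy assessments, so 10 after Day 1. If visits to week 96 are 24-weekly, as in Interviews, only weeks 24, 48, 72 and 96 remain on treatment. With Table 1's two off-therapy assessments that makes 6. The scores are repeated under either schedule.

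**Size of the precision loss**

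The plan gives no power or precision figure for these scores, so there is none to reproduce. Inputs:

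- Patients per arm: 245 × (1 − 0.20) = 196, from Sample size estimation.
- Two-sided alpha of 0.05, from Outcome analysis.
- Correlation r between the Day 1 and later score: not in the document, assumed at 0.3, 0.5 and 0.7.
- Normal scores with equal variance, one later visit.

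Formulas, with the variance of an unadjusted comparison of later means set to 1:

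- ANCOVA on Day 1: 1 − r².
- Change score: 2(1 − r).
- Large-sample efficiency of Wilcoxon against the t test under normality: 3/π = 0.955.
- Efficiency of Wilcoxon on raw scores against ANCOVA: 0.955 × (1 − r²).
- Efficiency of Wilcoxon on change scores against ANCOVA: 0.955 × (1 − r²) / [2(1 − r)] = 0.955 × (1 + r)/2.
- Standardised difference giving ANCOVA about 80% power: 2.8016 × √[(2/196)(1 − r²)].

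Power was then simulated at that difference (4,000 runs per r, standard error at most √(0.25/4000) = 0.8 percentage points).

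| | r = 0.3 | r = 0.5 | r = 0.7 |
|---|---|---|---|
| Standardised difference | 0.270 | 0.245 | 0.202 |
| Efficiency, Wilcoxon on raw score | 0.87 | 0.72 | 0.49 |
| Efficiency, Wilcoxon on change score | 0.62 | 0.72 | 0.81 |
| Power, ANCOVA | 79% | 79% | 79% |
| Power, Wilcoxon on raw score | 74% | 65% | 49% |
| Power, Wilcoxon on change score | 59% | 67% | 71% |

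Under both readings of what is ranked, the Wilcoxon test has less power than the baseline-adjusted comparison at each r tried.

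**The case against.** The strongest reply is that a general rule followed at once by a specific one is normally read as a rule and its exception, so the Wilcoxon test simply governs questionnaire scores. Another possible reading is that the mixed model describes the course over visits and the rank test a summary. A rank test is also defensible for bounded, possibly skewed scores, and covariates and target visits are commonly left to an analysis plan that is not shown here.

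Much of this stands. The text shows an unresolved overlap, and a reader who infers an outright contradiction goes further than it allows. Four other stronger readings also lack support:

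- **That the rank test ignores the Day 1 score.** The article does not say what is ranked, and a change score would use it, though less efficiently than adjustment.
- **That all three scores fall under both rules.** The TCM symptom score may not count as a questionnaire score. If so, only the mixed model applies to it.
- **That the 10 later visits add precision in any case.** A group-by-visit model with unstructured covariance and complete data (the Missing data section fills secondary data by last observation carried forward) gains essentially nothing from other visits for a contrast at one visit. A gain needs an average over visits, and sizing it needs assumptions on the correlation pattern and on a constant effect.
- **That a 95% interval is promised for each score.** The section sets only the confidence level, and a rank test could be reported with a Hodges-Lehmann shift and interval.

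The article also states no Day 1 covariate for its mixed model, so the gain shown above comes from the adjustment proposed here and not merely from dropping the rank test. What the reply does not remove is that the article names two between-group methods for SF-36 and CLDQ. Even as an exception, the rank test is the weaker use of the data.

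**Conclusion.** The point holds in limited form. For SF-36 and CLDQ, and possibly the TCM symptom score, the article does not fix one between-arm analysis. If the Wilcoxon test governs, the loss against single-visit ANCOVA at about 80% power is roughly 5 to 30 percentage points on raw scores (79% to 74%, and 79% to 49%). On change scores it is roughly 8 to 20 points (79% to 71%, and 79% to 59%). The direction is the same under both readings and at each correlation tried. The size is illustrative, since it rests on the assumed r, normal scores, one visit and 196 per arm. The loss should not be summarised by 1 − r² alone, because that ratio compares ANCOVA with unadjusted means and fits only the raw-score reading.

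Only secondary outcomes are affected, and the primary recurrence comparison is untouched.

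**What to change.** 1. Make the mixed model already planned, with the Day 1 score as covariate and a group-by-visit term, the single main between-arm analysis for SF-36, CLDQ and the TCM symptom score.
2. Name one main contrast, for example week 96 with off-therapy week 24 as supportive, and report it with a 95% CI. Two contrasts of equal rank would reopen the choice.
3. Keep the Wilcoxon test only as a sensitivity analysis for skewed scores. State the visit and the form of the score that it ranks, and define or delete the term total effect.
4. Reconcile the 24-weekly visits in Interviews with the 12-weekly schedule in Table 1, since these set the number of repeated scores.

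The cost is a few sentences of text and no new data. The downside is reliance on approximate normality of mean scores, which is minor at about 200 per arm and is covered by the sensitivity analysis.

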## Inclusion criteria

The inclusion criteria are as follows: (1) diagnosed CHB with positive HBeAg, who has experienced HBeAg clearance and/or seroconversion; (2) aged between 18 and 65; (3) TBIL < 3 × ULN; (4) HBsAg < 5000 IU/ml; (5) TCM symptoms are classified as stagnation of the liver and deficiency of Spleen Qi and Damp-Heat in the liver and gallbladder; and (6) voluntarily sign informed consent.

In the informed consent form, we explain the protocol and clearly inform the participants that after 96 weeks of consolidation therapy, they will stop NA treatment and be closely monitored for the next 24 weeks. Although the procedure complies with the AASLD [21], APASL [22], and EASL [23] guidelines for CHB treatment, there could be potential risks (including virological or clinical relapse) during the off-therapy period, and patients may be required to restart antiviral therapy. Patients are free to quit the trial any time before the off-therapy period.

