## Therapeutic regimen

Patients who meet the inclusion criteria will be allocated in a 1:1 ratio to either the experimental group (EG) or the control group (CG). Patients in the EG will receive TGBXJD granules along with ETV. Patients in the CG will receive TCM placebo along with ETV. The treatment duration is 96 weeks. Those who develop clinical relapse during consolidation therapy (in the first 96 weeks) will be switched to TDF (300 mg per day) according to the guidelines [25] and be removed from the study. All patients who meet the following NA withdrawal criteria in the first 96 weeks will stop their ETV treatment and will be closely monitored in the following 24 weeks: (1) serum ALT persistently within the normal range (under 40 IU/L) and (2) serum HBV DNA persistently undetectable (under 30 IU/mL). Once clinical recurrence is confirmed during the off-therapy period, antiviral treatment (entecavir, 0.5 mg per day) will be restarted immediately (Fig. 1).

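### Within-group before-after paired t tests share the p < 0.05 rule with the between-group tests and are not marked descriptive, although both arms take entecavir and the tests cannot isolate the granules

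*Protocol article*

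**What the plan says.** The Outcome analysis section of the protocol article gives a between-group method for each type of outcome:

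- Primary outcome: "the proportions of patients who developed off-therapy relapse in each group will be compared with the Pearson chi-square method".
- Secondary outcomes, treated as continuous: "we will use repeated-measures mixed effects models to test differences between the groups".
- Questionnaires: "The total effect of the scale scores from questionnaires will be tested with the Wilcoxon rank sum test".

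It then adds a test that does not compare the arms: a paired t "test will be used for comparisons of data before and after treatment within groups". The next sentence sets a single two-sided threshold, under which a p "value < 0.05 will be considered statistically significant". It neither exempts the paired tests nor calls them descriptive.

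On treatment, the Therapeutic regimen section gives entecavir to both arms for 96 weeks. The control arm is not untreated: "Patients in the CG will receive TCM placebo along with ETV".

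**The concern.** The trial's question is whether adding the granules changes outcome relative to adding placebo. The null hypothesis of a paired t test within one arm is that the mean change over time in that arm is zero. In the granule arm, that change combines 96 weeks of entecavir, the passage of time, placebo response, regression to the mean and whatever the granules do. Rejecting the null says that something changed, not that the granules changed it.

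Exposure is greatest for the TCM symptom score and the two quality-of-life scales (CLDQ and SF-36). They are patient-reported and measured repeatedly in both arms. Patients also enter with a defined symptom pattern: "TCM symptoms are classified as stagnation of the liver and deficiency of Spleen Qi and Damp-Heat in the liver and gallbladder".

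At stake are claims on the secondary outcomes. A significant before-after result with granules, or significance with granules but not with placebo, would meet the plan's stated criterion for significance without being evidence about the granules.

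**Working it through.** **The plan's own figure.** The article gives no expected change, SD or power for the paired tests, so there is nothing to reproduce. Only the number of patients is taken from the plan.

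**Inputs.**
- 245 per arm with a 20% loss considered (Sample size estimation): 245 × (1 − 0.20) = 196 evaluable per arm. Results for 245 are also shown, because carrying the last observation forward for secondary outcomes could keep more patients in the analysis.
- Two-sided 0.05 (Outcome analysis).
- Common drift d = mean change ÷ SD of change, the same in both arms, with no granule effect. This is an **assumption**, so a range is shown.

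**Formula.** The paired t statistic has n − 1 degrees of freedom and noncentrality λ = d√n. The chance of significance in one arm is p = P(|T| > t), where t is the 97.5% point of the central t distribution. With identical, independent arms, the chance that only the granule arm is significant is p(1 − p), which cannot exceed 0.5 × 0.5 = 0.25.

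**Numbers in, n = 196.** √196 = 14 and t is about 1.97.
- d = 0.10: λ = 1.4, p = 0.286; granule arm only 0.286 × 0.714 = 0.204.
- d = 0.14: λ = 1.96, p = 0.496; granule arm only 0.496 × 0.504 = 0.250.
- d = 0.20: λ = 2.8, p = 0.796; granule arm only 0.796 × 0.204 = 0.16.

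| Assumed d | One arm significant, n = 196 | One arm significant, n = 245 | Granule arm only, n = 196 | Granule arm only, n = 245 |
|---|---|---|---|---|
| 0 | 5% | 5% | 5% | 5% |
| 0.05 | 11% | 12% | 10% | 11% |
| 0.10 | 29% | 34% | 20% | 23% |
| 0.14 | 50% | 59% | 25% | 24% |
| 0.20 | 80% | 88% | 16% | 11% |
| 0.30 | 99% | 99.7% | 1% | 0.3% |

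The chance passes 50% at d of about 0.141 (n = 196) or 0.126 (n = 245). It reaches 80% at about 0.20 or 0.18.

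**Between-group check.** 5,000 trials were simulated for each scenario with the same drift in both arms (d = 0.1, 0.2, 0.3). A two-sample t test of change, standing in for the planned between-group methods, rejected in 4.7% to 5.1% of trials at either sample size. On the same data, the paired test in one arm rejected in 30%, 80% and 99% of trials (n = 196) and in 36%, 88% and 99.7% (n = 245).

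**The case against.** The strongest reply is that nothing in the section is false. A paired t test correctly answers the question put to it, whether an arm changed. If both arms truly change, its rejection is correct and not a false positive. Every outcome type has its own between-group method, and the article nowhere says that a within-group p value will support a claim about the granules. It is also a condensed article, and the full protocol or analysis plan may say how these results are to be read. Before-after description has a proper use here, for instance for liver biopsy and cccDNA, which are measured only at Day 1 and week 96.

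Much of this stands. It limits the point to how secondary results are tested and labelled. It does not remove it, because the article states the test and places it under the common significance rule.

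Several stronger readings are tempting, and the documents do not support them:

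- *The paired tests will usually be significant for any outcome that drifts.* At 0.05 to 0.10 SD the chance is only 11% to 34%. Patients have already reached HBeAg clearance and/or seroconversion at entry, so some viral markers may hardly move.
- *Discordant significance favours the granules in up to half of trials.* Significance in exactly one arm does reach 50%, but half of those cases are placebo-only. The pattern favouring the granules peaks at 25%.
- *Regression to the mean alone makes significance near certain.* That would need selection on a score cut-off. The inclusion criteria use a pattern classification, state no cut-off, and do not select on CLDQ or SF-36.
- *The t test clashes with the expected non-normal variables.* The Data description section says only how variables are displayed ("abnormally distributed continuous variables will be expressed as medians and interquartile ranges"). The paired test depends on the distribution of the differences, and with about 196 per arm moderate non-normality matters little.

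**Conclusion.** The point holds in limited form. The plan includes within-arm significance tests that cannot separate the granules from entecavir, time, placebo response and regression to the mean, and gives them the same threshold as the tests that can. Their chance of significance with no granule effect depends on a drift that the article does not state. It is modest for small drifts and passes one half only above about 0.13 to 0.14 SD of change. At its worst, a result favouring the granule arm alone arises in about one trial in four for a given outcome, against about one in twenty for a between-group test of change. These figures assume identical arms, normally distributed change and 196 to 245 patients per arm.

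The primary outcome, its chi-square test and the planned between-group tests are unaffected. A reader might infer that the sponsor intends to claim efficacy from before-after p values. The article does not say so; the fault is that the wording leaves it open.

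**What to change.** Replace the paired t test sentence in the Outcome analysis section with:

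*Change from Day 1 will be described within each arm by its mean or median with 95% CI, without significance testing; conclusions about the granules on secondary outcomes will rest only on the between-group comparisons, with the mixed models adjusted for the Day 1 value.*

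Leave the chi-square test of the primary outcome as it is. The Wilcoxon rank sum test for the questionnaires can also stay, since it is a between-group comparison. The restriction should name secondary outcomes explicitly: wording that put all inference on the mixed model would displace both of those tests.

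The change needs no new data or patients and takes no power from any comparison of the arms. The cost is the loss of before-after p values; the within-arm changes are still reported, with their precision.

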### Safety analysis

Safety analysis will be performed based on the subjects who actually received treatment. We will compare the data with Student’s *t* test or the Mann–Whitney *U* test. In addition, abnormal results from safety assessments will be further classified as “abnormal (no clinical significance)” and “clinically abnormal.” The latter will be inspected to determine they were caused by the trial drugs. The incidence of AEs will be described, and the specific grades of all the AEs in each group and their relationships with drugs will be described in detail. The proportions of patients who developed AEs between groups will be compared with Pearson’s chi-square test.

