## Safety monitoring

Primary vital signs and laboratory parameters will be assessed in patients regularly. Primary vital signs include body temperature, blood pressure, heart rate, and respiratory rate. Laboratory tests include routine blood, urine, and stool tests, along with fecal occult blood tests, ECG, and abdominal B ultrasound scan. In particular, relapse after drug discontinuation is defined as an HBV DNA level > 2000 IU/mL with a serum ALT > 2 × ULN.

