## Discussion

HBV infection remains a major global health concern, as the disease itself and its complications, mainly hepatocellular carcinoma and cirrhosis, caused 887,000 deaths in 2015 alone [26]. Currently, therapeutic drugs for CHB are limited to two types of NAs and interferon. Nucleotide drugs can inhibit virus replication for a long time, but they cannot prevent the synthesis of cccDNA [27], so it is still challenging to achieve clinical cure. Functional cure refers to a continuously negative HBV DNA level and negative conversion or seroconversion of HBsAg, but it can only be realized in a few patients. A systematic evaluation of 34 published studies involving 42,588 patients showed that the annual clearance rate of HBsAg in CHB patients was approximately 1% (including treated and untreated populations) and that in HBeAg-negative patients and HBeAg-positive patients, it was 1.33% (95% CI, 0.76–2.05) and 0.40% (95% CI, 0.25–0.59), respectively [28]. Therefore, lifelong medication is required for most patients. However, long-term treatment with nucleotide drugs has problems that cannot be ignored. Although the rates of resistance to ETV and TDF are low, the likelihood that a patient will develop resistance in the future is unclear. In addition, the high economic burden brought by long-term oral drugs is a vital trade-off factor. The withdrawal of NAs can significantly reduce expenditures for medical care and public health. Additionally, the side effects of NAs cannot be neglected [29], such as the renal toxicity and skeletal toxicity of the first-line therapeutic drug TDF. The new drug TAF bypasses this problem, but its cost is high; thus, the drug has not been widely applied in many countries.

In recent years, some scholars have proposed the concept of immune control, in which the host’s immune system still exerts significant and explicit control over HBV after drug withdrawal; thus, HBV DNA remains at an immeasurable level, and no virology or clinical relapse will occur for a long time after drug withdrawal (beyond 6 months). Therefore, long-term virology inhibition after the withdrawal of nucleotide drugs can be regarded as a possible endpoint of therapy. According to the APASL guidelines, HBeAg-positive patients can discontinue drugs under monitoring by strict follow-up visits after the serological conversion of e-antigen and consolidation therapy for 12 months [22].

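### The safety section compares measurements between arms only by tests of location, states no between-arm comparison of clinically abnormal results, and leaves liver and renal function off its named safety tests

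*Protocol article*

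**What the plan says.** **Between-arm comparison.** The Safety analysis section of the protocol article uses the subjects who received treatment and says "We will compare the data with Student’s *t* test or the Mann–Whitney *U* test". It gives no rule for choosing between the two tests.

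**Abnormal results.** In the same section, "abnormal results from safety assessments will be further classified as" either without clinical significance or clinically abnormal. Of the second class it says "The latter will be inspected to determine they were caused by the trial drugs". No comparison of the two arms on this class is stated.

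**Adverse events.** The section also plans that "the specific grades of all the AEs in each group and their relationships with drugs will be described in detail", and that "The proportions of patients who developed AEs between groups will be compared with Pearson’s chi-square test".

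**Which tests count as safety tests.** The Safety monitoring section says "Laboratory tests include routine blood, urine, and stool tests, along with fecal occult blood tests, ECG, and abdominal B ultrasound scan". ALT appears there only within the definition of relapse. Table 1 (Assessments) schedules liver and renal function at Day 1 and weeks 24, 48, 72 and 96, and again off therapy, and the sentence introducing the table gives safety as one of its purposes. The Secondary outcomes section says "Secondary outcome measurements include virus serological indicators, HBV DNA, liver function, liver biopsy results" and continues with virological, symptom and quality-of-life measures. Renal function is not among them.

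**The concern.** Organ toxicity usually shows as large changes in a minority of patients, not as a shift of the whole group. A rank test counts a very high value only as one more high rank, so it hardly responds to a small tail. The clinically abnormal class is the quantity that would show such a tail, and it is reviewed patient by patient without a stated comparison of arms. In chronic hepatitis B a single ALT rise is hard to attribute to a cause, so an imbalance between randomised arms is more informative than individual causality judgements.

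The incomplete list adds to this. The abnormality classification applies to safety assessments, and two organ-function panels are not named as such. Liver function is instead a secondary outcome, which the Outcome analysis section treats as continuous and gives to a mixed model. An ALT rise with HBV DNA at or below 2000 IU/mL is not a clinical recurrence under the Primary outcomes definition. It could therefore enter only a model of means unless someone records it as an AE. At stake is whether 96 weeks of granules can be described as having no difference in laboratory safety when clinically abnormal results were in fact more frequent on them.

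**Working it through.** The safety section states no figure to reproduce. The check has two parts.

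**1. Where each panel is assigned**

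| | Table 1 | Safety monitoring list | Secondary outcomes | Stated analysis |
|---|---|---|---|---|
| Blood, urine, stool | yes | named | no | t test or Mann-Whitney; abnormality review |
| Liver function | yes | not named | named | mixed model |
| Renal function | yes | not named | not named | none assigned |

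**2. What the stated tests can detect**

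Inputs: 245 per arm (Sample size estimation); two-sided 0.05 (Outcome analysis). The protocol gives no toxicity rates, so these are *assumed*: each patient's worst ALT is log-normal with median 22 IU/L and log SD 0.4; affected patients lie uniformly between 100 and 300 IU/L; the abnormality threshold is 80 IU/L, twice the 40 IU/L normal limit given under Therapeutic regimen.

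*Mann-Whitney by hand, 6% v 1% affected.* If affected values exceed all unaffected ones, the chance that a granule patient's value exceeds a control patient's is

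0.06 × 0.99 + ½ × (0.94 × 0.99 + 0.06 × 0.01) = 0.0594 + 0.4656 = 0.525.

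The null value is 0.5, with standard error √[(2 × 245 + 1)/(12 × 245²)] = 0.0261. The expected z is 0.025/0.0261 = 0.96, which gives power of about 16%. However high the affected values are, this does not rise.

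*Simulation, worst value per patient, 245 per arm* (rounded; repeat runs differ by a point or two):

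| Affected (granule v control) | Mann-Whitney | t test | Fisher on proportion > 80 IU/L |
|---|---|---|---|
| 5% v 1% | 12–13% | 69% | 67% |
| 6% v 1% | 16–17% | 82–83% | 82–84% |
| 8% v 2% | 21% | 82–84% | 84% |

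If each event is visible at only one of the four on-treatment visits and arms are compared visit by visit (6% v 1%), power is about 5% for Mann-Whitney and 18% for the t test. The protocol specifies neither a worst-value nor a per-visit analysis.

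*Small counts, k v 0 at 245 per arm.* The power columns come from a separate simulation with log SD 0.35 and affected values of 120–400 IU/L.

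| Cases | Mann-Whitney power | t test power | Pearson p | Fisher p |
|---|---|---|---|---|
| 3 v 0 | 5% | 14% | 0.082 | 0.249 |
| 5 v 0 | 6% | 58% | 0.025 | 0.061 |
| 8 v 0 | 9% | 99% | 0.004 | 0.007 |
| 10 v 0 | 12% | about 100% | 0.001 | 0.002 |

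Mann-Whitney is weak throughout. The t test is weak at 3 cases but not at 8 or more. At 3 v 0 a test on counts does not reach significance either.

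**The case against.** A reader might infer that safety is judged by the t test or Mann-Whitney test alone, so that organ toxicity would be reported as no difference. The document does not support that:

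- The same section plans the abnormality classification, causality review, AE grades and drug relationship by group, and a chi-square test on AEs. The Adverse events section covers any AE, and a data monitoring committee may stop the trial for unexpected adverse reactions.
- The Data description section gives categorical variables as numbers and percentages, so counts of clinically abnormal results may well be tabulated. What is not stated is a comparison of arms.
- The Safety monitoring list is worded as inclusive, not exhaustive, and Table 1 has a stated safety purpose. The omission does not prove that liver and renal function would be left out of safety review.
- The t test is permitted, and on worst values it matches Fisher's test. That skewed ALT would go to Mann-Whitney is plausible but not stated.
- 6% v 1% of 245 is about 15 v 2 patients, many of whom would probably surface in case review. For a true handful, the proposed count test fails too.

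A reader might also take the Discussion's remark on renal and skeletal toxicity as a sign of risk from the granules. It concerns TDF and gives no such support.

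These points remove the claim that toxicity would be hidden. What stands is narrower. Renal function has no assigned role, liver function is not named as a safety measure, and the class best suited to show an excess has no stated between-arm comparison. The AE chi-square test reaches a laboratory abnormality only if it is recorded as an AE, and as written it pools all AEs, which dilutes an excess in one organ.

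**Conclusion.** The concern holds in limited form. The assessment schedule, the secondary outcomes and the safety list do not agree on liver and renal function, most clearly for renal function, and this rests on the text alone. The weakness of the stated comparison is conditional: if skewed measurements go to Mann-Whitney, a moderate excess such as 6% v 1% would be detected about one time in six, against about five in six for a comparison of proportions already available from the planned classification. Those figures rest on the assumed ALT distribution, event rates and use of worst values. They do not show that harm would be missed, because case review and AE reporting run alongside, and at about 3 v 0 cases that review is the only effective safeguard.

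**What to change.** 1. Reconcile Table 1, Secondary outcomes and Safety monitoring by naming liver and renal function as safety assessments. Liver function can remain a secondary outcome as well.
2. In Safety analysis, add for each test the number and proportion of treated patients per arm with at least one new on-treatment clinically abnormal result, whatever its attributed cause. Give the risk difference with 95% CI, with Fisher's exact test as support. Keep the stated t test or Mann-Whitney comparison and the case review beside it.

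The cost is a few lines of text and a few more safety tables, from data and a classification already planned. Comparing several tests will produce some chance differences, so the estimates and intervals should carry the interpretation. No treatment or clinical rule changes.
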